# Prospective cohort study of unselected nulliparous women with a nested randomised controlled trial of screening using the sFLT1:PlGF ratio, ultrasound and maternal characteristics and intervention using enhanced monitoring and early delivery: study protocol for the POPS2 cohort and randomised controlled trial

**DOI:** 10.1136/bmjopen-2026-122043

**Published:** 2026-08-07

**Keywords:** OBSTETRICS, Mass Screening, Randomized Controlled Trial

## Abstract

**Introduction:**

Current UK guidelines recommend measurement of symphyseal fundal height and measurement of maternal blood pressure and urinalysis, with the aim of detecting women at increased risk of fetal growth restriction (FGR) and pre-eclampsia. Between 2008 and 2013, we conducted a prospective cohort study recruiting 4512 nulliparous women at the Rosie Hospital, Cambridge, where we performed serial ultrasonic imaging and serial blood sampling and generated a novel screening test for pre-eclampsia and FGR. The method involved measuring the ratio of two placental biomarkers (soluble fms-like tyrosine kinase receptor-1 and placenta growth factor) at ~36 weeks of gestational age (wkGA) and combining the result with maternal characteristics and ultrasonic imaging. Women who screened positive had a ~50% risk of a composite outcome, consisting of pre-eclampsia±delivery of a baby with a birth weight <3rd percentile for sex and gestational age±perinatal morbidity or death. It is plausible that screening and intervention using this method might improve pregnancy outcome.

**Methods and analysis:**

Nulliparous women with an apparently normal singleton pregnancy will be recruited at their dating ultrasound scan. Blood will be obtained at this visit, at their anomaly scan (20 wkGA), and at two research appointments (28 wkGA and 36 wkGA) when research ultrasound scans will be performed. Blood for DNA will be obtained from the father of the baby where possible and the placenta will be sampled following birth. At 36 wkGA, women will be consented for participation in the randomised controlled trial (RCT) element of the study and their risk of term pre-eclampsia and FGR will be assessed using the novel approach. Women who screen high-risk will then be randomly allocated to either having the result revealed or masked. Women randomised to having the result revealed will be offered early delivery and/or enhanced monitoring. Where the result is masked, there will be no communication between the research team and the participant, and she will continue to receive routine care at the Rosie Hospital. The primary outcome is a composite of pre-eclampsia, FGR and perinatal morbidity and mortality. The study will also generate data and biological samples to support future research in novel screening methods and disease mechanisms.

**Ethics and dissemination:**

The study received ethical approval from the East of England Research Ethics Committee. All women provide written informed consent to participate in the cohort. Women provide a second written informed consent to participate in the RCT. The study results will be disseminated by presentation at international conferences and publication in peer reviewed journals.

**Trial registration number:**

ISRCTN1218142.

STRENGTHS AND LIMITATIONS OF THIS STUDYThe power calculation is informed by a previous non-interventional cohort study.The study design allows separate assessment of the prognostic test accuracy of the screening test and the clinical effectiveness of the intervention.The study will generate an extensive biobank which will facilitate the identification of novel methods of screening with enhanced predictive performance.The study is confined to a single centre, which allows implementation of the screening programme with high fidelity, but may reduce the generalisability of the results.The study only addresses screening nulliparous women.

## Introduction

### Background and rationale

 Maternal and perinatal deaths account for 6%–7% of all deaths globally, approximately equivalent to half of the global burden of deaths caused by cancer.^1^ Placental dysfunction is implicated in the aetiology of many of the associated conditions, including pre-eclampsia, fetal growth restriction (FGR), spontaneous preterm birth and stillbirth.^2^ The approaches to screening for these outcomes include methods which are relatively crude and ineffective. For example, the UK’s National Institute for Health and Care Excellence (NICE) recommended method of screening for FGR is to measure the external size of the uterus with a tape measure, despite the fact that surveillance based on this approach has a sensitivity to detect small infants of ~20%.^3^ An alternative is to perform late pregnancy ultrasonic fetal biometry in all women. However, a meta-analysis of eight randomised controlled trials (RCTs) of universal ultrasound recruiting ~35 000 women showed no evidence of benefit.^4^ Implementation of universal late pregnancy ultrasound in France was associated with dramatic increases in morbidity in false positives, principally through iatrogenic prematurity.^5^

In a 2012 review in *PLoS Medicine*,^6^ we outlined key methodological weaknesses in the literature:

Screening tools were evaluated in interventional trials in the absence of high quality information on their diagnostic effectiveness.Screening tests were not coupled to an effective intervention.Trials were underpowered.

The review proposed a plan to generate novel clinically effective methods of screening:

Trials should be preceded by high quality studies of diagnostic effectiveness.Initial efforts should focus on screening for complications at term.The most efficient trial design is to screen all women and randomise high-risk women to intervention or routine care.Initial efforts should focus on nulliparous women,^7^ as they have a higher a priori risk of adverse pregnancy outcome. They lack information on complications during previous pregnancies,^8^ one of the most discriminating predictors of pre-eclampsia and FGR.

In 2007, we designed the Pregnancy Outcome Prediction Study (POPS), a prospective cohort study of nulliparous pregnant women in the Rosie Hospital, Cambridge. The protocol has been published,^7^ the first output of the study described the conduct of the cohort,^3^ and a review article describes the biological samples.^9^ The study followed the first part of the plan outlined in the *PLoS Medicine* review and has generated a screening test for complications at term. Combining the data from two previous publications arising from the POPS cohort,^10
11^ we have created a screening test (described in detail below) which is conducted at around 36 weeks of gestational age (wkGA) and has a high positive predictive value, but has a sensitivity of less than 50%. This means that, while screening and intervention may be beneficial for individual women, better tests are required to yield substantial reductions in the population incidence. Moreover, POPS2 is confined to screening and intervention for pre-eclampsia and FGR near term and does not address the problem of pre-eclampsia and FGR associated with preterm birth. Women who are identified as high-risk at 28 wkGA have an absolute risk of preterm delivery of a small infant of about 20%.^11^ Hence, for one true positive there would be four false positives. Consequently, use of this test at 28 wkGA has the potential to cause net harm through iatrogenic prematurity in the false positives. This background information informs the objectives of the study.

### Objectives

We aim to perform a nested RCT within a prospective cohort study of nulliparous women with a singleton pregnancy to determine (a) whether screening and intervention using a novel method for assessing the risk of pre-eclampsia and FGR at term correctly identifies women at increased risk of complications, and (b) whether intervention in high-risk women improved the outcome for the mother and/or infant. Our secondary aim is to use the data and biological samples from the cohort study to generate better performing screening tests for pre-eclampsia, FGR and other adverse outcomes of pregnancy. The secondary aim will address the two weaknesses described above, namely, the less than 50% sensitivity of our current test to detect pre-eclampsia at term and the absence of screening tools with a high positive predictive value for pre-eclampsia and FGR resulting in preterm birth. However, we believe that the current screening test has the potential to prevent adverse outcomes using technology that is currently available and licensed for clinical use. Given that it could take many years to develop, validate and obtain regulatory approval for novel tests, we believe an RCT of our existing method is justified now. A further goal of the extensive collection of biological samples is to use these to better understand the associations and mechanisms linking pregnancy to health and disease in the mother and offspring.

## Methods and analysis

### Trial design

The study is a prospective cohort study with a nested, parallel group RCT where women screening high-risk will be allocated in a 1:1 ratio to intervention or routine care, to test the superiority of intervention among women who screen high-risk.

### Study setting

The study will take place at a single centre, The Rosie Hospital, Cambridge, UK, which is an academic maternity hospital providing care for about 5000–6000 deliveries per annum, serving the local population of Cambridge as well as providing tertiary level obstetric, maternal-fetal medicine and neonatal care for hospitals in the East of England, UK.

### Eligibility criteria

#### Cohort study

Eligible women will be those who are nulliparous (no previous births >23 wkGA), with a single viable fetus at the dating ultrasound scan with an ultrasonic estimated gestational age <18 wkGA. Exclusion criteria for the cohort study will be those who are unable to provide consent, maternal age of <16, previous births >23 wkGA, multiple pregnancy and a non-viable fetus or a fetus with a major anomaly or nuchal translucency >3.5 mm at the time of the dating ultrasound.

#### Randomised controlled trial

The RCT is nested within the cohort, that is, all women participating in the RCT will be cohort members, but not all cohort members will participate in the RCT. Inclusion criteria for the RCT are women who were recruited to the cohort study and who attended for their 36 wkGA visit. Exclusion criteria are (a) participants where the 36 wkGA research scan demonstrated one of the findings which mandates that the result would be revealed (see below), (b) any participant not planning to deliver at the Rosie Hospital or (c) any participant who had already been offered a date for medically indicated delivery within 7 days of their 36 wkGA visit.

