### Outcomes

The study has two primary outcomes and both are composites. The first is one or more of the following: (a) diagnosis of pre-eclampsia (using the ACOG 2013 definition^12^), (b) perinatal death or perinatal morbidity or (c) delivery of an infant with a birth weight <3rd percentile for sex and gestational age. Perinatal death is defined as stillbirth or neonatal death. Perinatal morbidity is defined as one or more of the following: a 5 min Apgar score <7, delivery with metabolic acidosis (defined as an umbilical cord artery or vein pH<7.1 and a base deficit of >10 mmol/L) or admission to the neonatal unit (defined as admission <48 hours after birth and discharge ≥48 hours after admission), that is, either the special care baby unit (SCBU) or the neonatal intensive care unit (NICU). The second primary outcome is a subgroup of the first and is defined as one or more of the following: (a) pre-eclampsia with severe features (ACOG 2013 definition^12^) or (b) perinatal death or severe perinatal morbidity. Severe perinatal morbidity is defined as live birth associated with hypoxic ischaemic encephalopathy (any grade), use of inotropes, mechanical ventilation or severe metabolic acidosis (defined as an umbilical cord artery or vein pH<7.0 and a base deficit of >12 mmol/L).

Secondary outcomes will include each of the individual elements of the maternal and perinatal composite described above. The following additional secondary outcomes will be studied, based on a previous trial of term induction of labour, the 35/39 trial.^13^

Maternal: (a) maternal death, (b) maternal stroke, (c) maternal admission to any medical unit (eg, intensive care unit, stroke unit, coronary care unit, neurosciences critical care unit), (d) placental abruption, (e) cord prolapse, (f) caesarean section, (g) epidural anaesthesia, (h) instrumental vaginal delivery, (i) general anaesthesia, (j) postpartum haemorrhage (any >500 mL), (k) postpartum haemorrhage requiring blood transfusion, (l) infection (pyrexia >38°C and treated with a course of antibiotics).

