**Figure 2 F2:**
[figure not shown]
Flow diagram of risk assessment and randomisation. Percentages in blue boxes indicate the observed proportion in the original POP study. The yellow box indicates an estimated risk of the primary outcome among the women who screen high-risk and are offered induction of labour. EFW, Estimated fetal weight; GA, gestational age; PlGF, placenta growth factor; sFLT1, soluble fms-like tyrosine kinase receptor-1.

**Table 1 T1:** Schedule of enrolment, interventions and assessments for the randomised controlled trial

	Trial period			
**Timepoint**	**35–37 wkGA** (**date of visit=t1**)	**Within 4 days of t1**	**Within 9 days of t1**	**Post-delivery**
Enrolment				
Clinical assessment*	X			
Ultrasound scan	X			
Phlebotomy	X			
Eligibility screen	X			
Informed consent	X			
Risk assessment				
Measurement of sFLT1:PlGF		X		
Assessment of high-risk status		X		
Randomisation of high-risk women		X		
Intervention/comparator				
Intervention†			X	
Comparator (routine care)				
Assessment				
Outcome collection				X

* Clinical assessment included confirming the presence or absence of maternal characteristics used in the risk assessment and confirming that there was no plan in place for delivery within the next 7 days.

† Intervention consists of a face-to-face assessment with a maternal-fetal medicine specialist and a plan for medically indicated delivery and/or enhanced monitoring is made.

PlGF, placenta growth factor; sFLT1, soluble fms-like tyrosine kinase receptor-1; wkGA, weeks of gestational age.

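### Pre-eclampsia diagnosed before the 36-week visit or before randomisation is neither an exclusion nor separated in the outcome, so PPV is inflated and the relative risk may be diluted

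*Protocol article*

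**What the plan says.** **Eligibility.** Under Eligibility criteria, Randomised controlled trial, the protocol article states: "Inclusion criteria for the RCT are women who were recruited to the cohort study and who attended for their 36 wkGA visit". There are three exclusions:

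- "participants where the 36 wkGA research scan demonstrated one of the findings which mandates that the result would be revealed";
- not planning to deliver at the study hospital;
- "any participant who had already been offered a date for medically indicated delivery within 7 days of their 36 wkGA visit".

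The reveal findings listed under Visit 4 are all ultrasound findings.

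**Checks before randomisation.** Table 1 places the visit at "35–37 wkGA (date of visit=t1") and allows randomisation up to 4 days later. Its footnote describes the clinical assessment as confirming the maternal risk characteristics and "confirming that there was no plan in place for delivery within the next 7 days". Under Implementation, the check made before randomisation concerns high-risk status.

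**Outcome.** The first component of the first primary outcome is "a) diagnosis of pre-eclampsia (using the ACOG 2013 definition"). The second primary outcome uses pre-eclampsia with severe features. Neither has an onset condition. The only time anchor, at the end of the Outcomes section, ties all diagnoses to the delivery admission.

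**Use.** The strengths list claims "separate assessment of the prognostic test accuracy of the screening test". The same outcome serves both the screening-performance analysis and the intention-to-treat RR.

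**The concern.** Take a woman whose pre-eclampsia was diagnosed before the visit and who has not been offered a medically indicated delivery within 7 days. None of the three exclusions applies to her, and none of the described checks would find her. If her disease persists to delivery, the delivery-admission anchor does not remove her from the outcome.

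Two things follow if she screens positive.

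- **Screening performance.** She is scored as a correct prediction by a blood sample taken after her diagnosis. Randomisation gives no protection here, because the analysis compares masked high-risk women with low-risk women.
- **Effectiveness.** She is an event of the first primary outcome whichever arm she enters. A diagnosis made in the gap of up to 4 days between visit and randomisation has the same effect on this comparison, although for screening it is a genuine later event. For the second primary outcome she is a fixed event only if severe features were already present.

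The Discussion relies on these two results to tell failure of the test from failure of the intervention, so an inflated PPV and a diluted RR would both point towards blaming the intervention.

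**Working it through.** **Inputs (Sample size section).** In the earlier cohort, 126 of 256 high-risk women (49%) had the primary outcome. Of these 126 events, 51 were taken as preventable, leaving 75. The updated plan has 250 high-risk women (125 per arm) and a two-sided threshold of 0.025.

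**The plan's own figures.** I used the two-proportion normal approximation with pooled variance under the null and no continuity correction.

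- 49% vs 29%, alpha 0.05, 90% power: 123 per arm, 246 in total (stated 246).
- 184 women, alpha 0.05: power 79.9% (stated about 80%).
- 250 women, alpha 0.025: power 84.7% (stated 85%).
- RR = 75/126 = 0.595 (stated about 0.6).

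All reproduce. With the unrounded 126/256 and 75/256, power at 250 women and alpha 0.025 is 84.3%, which is the base for the table.

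**Assumption.** The protocol does not say how many high-risk women already have pre-eclampsia. Let f be that share, all of them among the 126 events, with f = 2%, 5% or 8% as illustrative values.

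**PPV without these women** = (0.49 − f)/(1 − f):

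- f = 2%: 0.47/0.98 = 48.0%
- f = 5%: 0.44/0.95 = 46.3%
- f = 8%: 0.41/0.92 = 44.6%

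**RR and power.** The result depends on how much prevention the plan had already credited to these women. For the 37-week induction group, the Sample size section credits 25% of pre-eclampsia before 38 weeks. For the 39-week group it credits none before 39 weeks. If a credit c was given to cases that cannot be prevented, the intervention-arm events become 75 + c × f × 256, and RR = (75 + c × f × 256)/126.

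| f | Cases (f × 256) | c = 25%: RR | c = 25%: power | c = 0: RR | c = 0: power |
|---|---|---|---|---|---|
| 2% | 5.12 | 76.28/126 = 0.605 | 82.1% | 0.595 | 84.3% |
| 5% | 12.8 | 78.2/126 = 0.621 | 78.5% | 0.595 | 84.3% |
| 8% | 20.48 | 80.12/126 = 0.636 | 74.5% | 0.595 | 84.3% |

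With c = 0 nothing moves, because the plan already treats these cases as unpreventable.

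**The case against.** **The delivery-date exclusion already deals with this.** In part. It removes diagnosed women who have been offered delivery within 7 days, but it acts on a date, not on a diagnosis.

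**The analysis plan may restrict the outcome to new onset.** It may, and it is not shown here. But the eligibility list belongs to the protocol and is given in full, and the outcome definition is given in detail without an onset condition.

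**The numbers may be very small.** This stands. At 2%, PPV moves by about 1 percentage point and the RR by 0.01 at most under the 25% credit. A reader might take the pre-eclampsia trial cited under Adverse event reporting as evidence that expectant management is common at this stage. That trial is cited only for its definition of unexpected serious adverse events, and says nothing about practice at this hospital.

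**A larger power loss might be inferred.** Applying the average prevention of 51/126 (about 40%) to the existing cases would give, at 5%, an RR of 0.64 and power of 74%. That presumes the plan credited them with about 40% prevention. The Sample size section does so only for cases with growth restriction in the 37-week group.

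**The treatment comparison might be thought biased.** It is not, on average. Allocation is randomised and stratified, so existing cases should balance, and what remains is possible dilution towards 1.

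**Existing cases could simply be dropped from the primary analysis.** That would depart from the stated intention-to-treat analysis late in recruitment, and the documents do not support it as the primary approach.

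**Conclusion.** The gap is real. As written, the eligibility list, the checks and both outcome definitions let pre-eclampsia present before the visit or before randomisation count towards the primary outcomes.

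The firmer consequence is for screening. PPV is biased upwards, and accuracy described as prognostic is partly diagnostic. Under assumed shares of 2% to 8%, the excess is about 1 to 4 percentage points on 49%. A reader might infer that sensitivity is inflated as well, but its direction depends on how existing cases split between screen-positive and screen-negative women, which the documents do not give.

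For effectiveness, the consequence ranges from nothing to modest dilution: an RR between 0.595 and about 0.64, and power between 84.3% and about 74.5%, depending on the share and on the credit already given. The stated sample size arithmetic is correct. Every size quoted rests on an assumed frequency, which the investigators could replace with a count from dated records.

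**What to change.** Settle the following before unblinding.

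1. **Screening performance.** Count only pre-eclampsia that first meets the trial's ACOG 2013 definition after the 36-week visit, and leave out women with a documented earlier diagnosis, whether they screened high or low risk.
2. **Effectiveness.** Keep the all-randomised intention-to-treat analysis as primary. Add a prespecified sensitivity analysis excluding women with pre-eclampsia documented before randomisation, identified from dated records without reference to arm.
3. **Women still to be enrolled.** State whether pre-eclampsia already diagnosed at the visit is an exclusion, and check the point again just before randomisation. Cohort recruitment ceased on 5 June 2026 and trial recruitment ends about 6 months later, so this reaches only the last participants. If eligibility changes, it needs an amendment with ethics and sponsor review.

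The cost of items 1 and 2 is a small date-checking task in records the trial already extracts, and a slightly lower reported PPV.

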### Who will recruit participants and document their consent?

#### Cohort

In the Rosie Hospital, women who require a dating ultrasound scan will be identified either by receipt of a ‘Notification of Pregnancy’ form or when a woman has confirmation of pregnancy in primary care and contacts the hospital to arrange a dating scan. The patient information leaflet will be sent with the appointment details.

The dating scan will be performed as routine. Any adverse findings on scan, for example, delayed miscarriage or suspected fetal abnormality, will follow the normal referral pathway. The sonographer conducting the scan will confirm that the woman has not had a previous birth beyond 23 wkGA and that she has a viable singleton pregnancy <18 wkGA at the time of the scan. The sonographer will ask the woman if she is happy to meet with the member of the research team to discuss the study. If they agree, the sonographer will inform the research staff that the woman is potentially interested in participating.

Women will also be alerted to the study through other means. This will cover the situation where the timing of the research scan lists was inconvenient. For example, we will place posters in prominent areas of the Rosie Hospital, including the ultrasound department, we will put a notice on the Rosie Hospital website, and we will also use social media sites (such as Facebook and X (previously Twitter)) to disseminate this information. These notices will alert women who were not approached for recruitment at the time of their dating ultrasound and provide the contact details for them to get in touch and arrange an appointment to come and discuss the study. Moreover, the patient information leaflet will be sent to all eligible women and it will detail how they can participate in the study if they are not approached at the time of the dating ultrasound.

Consent (form presented in online supplemental additional file 1) will be given following discussion of the study with an appropriately trained member of staff, such as a research midwife, research nurse or research sonographer.

The following are some of the key points to be raised during the consent process:

Participation in the study is voluntary, consent can be withdrawn at any time during the study and withdrawal will not affect their routine care.The purpose of the study.The requirements of participating in the study.That women will not be informed of the results of the 28 wkGA and 36 wkGA scans except for intra-uterine fetal death, previously undiagnosed and clinically relevant congenital anomaly, severely reduced amniotic fluid level, placenta praevia, grossly abnormal umbilical blood flow and non-cephalic presentation (36 wkGA).All information will be treated as strictly confidential.These analyses could include genetic studies and studies done by commercial entities.Participation in the study will not affect their routine care, except that they will be referred for assessment by the medical team if either of the scans demonstrated one of the findings described above.That they will be asked at the time of their 36 wkGA visit whether they want to participate in the RCT. This will involve giving them a patient information leaflet at their 28 wkGA visit, discussing the information on it, and signing a consent from at their 36 wkGA visit. The conduct of the RCT is described below.

Information relating to data handling and biological samples is detailed below.

The signed consent form has three copies, one will be retained for the study records, one placed in the patient’s hand-held notes and the third scanned for recording in the hospital’s electronic medical record (EMR, specifically the EPIC system). A letter will be sent to the woman’s GP informing them of participation in the study.

When women give consent, they will be directed to the NIHR Cambridge Clinical Research Facility for blood samples to be obtained (see below) and to make their next appointment.

